### Interventions

Participants will be randomised to receive two doses of either human immunoglobulin (intervention group) or placebo (control group), in addition to standard therapy (see Methods: assignment of intervention). There will be no set trial definition of standard therapy and this may vary between hospitals since there are currently no established national clinical care pathways for these. Participants will receive 1 g/kg/dose, in weight-based dosing bands (see online supplementary table S2). The IVIG product is Privigen (CSL Behring), supplied in unlabelled as 10 g/100 mL vials. Privigen is a licensed product, further details are outlined in the Product Information^21^ and the Summary of Product Characteristics (https://www.medicines.org.uk/emc/medicine/21359). The placebo is 0.1% Human Albumin Solution (HAS) in 0.9% Sodium Chloride solution which will be manufactured in the Aseptic Production Unit (APU), Pharmacy department, Royal Liverpool and Broadgreen Hospital, Liverpool, UK under cGMP conditions, under its MIA (IMP) licence and also supplied as 100 mL vials. The placebo has been constituted using HAS so as to prevent unblinding.

Packaging and labelling of both trial treatments will also take place at the same location. Labelling, which is identical for both trial treatments, has been approved by the Medicines and Healthcare products Regulatory Authority (MHRA) and conform to Annexe 13 of Good Manufacturing Practice standards and Article 13.3 of Directive 2001/20/EC (http://ec.europa.eu/health/files/eudralex/vol-4/2009_06_annex13.pdf). The APU will provide Qualified Persons services and distribute both trial treatments to the Clinical Trials Pharmacy at each recruiting site where they will be stored under controlled conditions and from where they will be dispensed.

The trial treatment will be prescribed on the participant's drug chart by a clinician who has been delegated for this task and using the suggested wording ‘Immunoglobulin/Placebo for the IgNiTE trial’. In addition, a clinical trials prescription form will be completed. For effective management of the trial treatment stock, and to minimise wastage, individual doses may vary slightly. A dosing guide for participants ≥13.5 kg is provided in a Clinical Study plan and is shown in online supplementary table S2. Participants <13.5 kg will receive 1 g/kg, rounded to the nearest whole gram.

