### Blinding

IgNiTE is a double-blind trial and a rigid blinding process will be in place throughout the trial to ensure validity of the data collected. Participants and their parents/guardians/legal representatives as well as all research staff involved in any aspect of the trial conduct, including recruitment, administration of trial treatment, carrying out trial assessments, data collection and entry, sample and statistical analyses, will be blinded to treatment allocation throughout the entire trial period. There will be separate monitors for blinded and non-blinded data. The active treatment and placebo will be visually identical (packaged and labelled in the same manner) and administered at the same dose and infusion rate to maintain blinding. To be able to manage trial treatment stock effectively and minimise wastage, the clinical trials pharmacists at each recruiting site who are independent of the trial will be non-blinded. The tear off section of the label will inform the dispensing pharmacist of the true nature of the contents (IVIG or placebo). At dispending, this section of the label will be removed to maintain blinding.

Unblinding of treatment allocation will occur only in exceptional circumstances when knowledge of the actual treatment received is absolutely essential for further management of the participant. Unblinding will be performed via the online randomisation system. The decision to unblind a participant's treatment allocation will be solely that of the site investigator. Only individuals given access to unblind will be able to do this and will include the site pharmacist, principal investigator and coinvestigators. Where there is a problem with Sortition, unblinding will be available via either the site pharmacist (during work hours) or a non-blinded staff member in Oxford (out of hours) who is independent of the trial, both of whom will have secure access to the master randomisation list for this purpose.

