### Harms

International Conference on Harmonisation (ICH) definitions are used for AEs, adverse events of special interest (AESIs), adverse reactions (ARs), serious AEs (SAEs), serious adverse reactions (SARs) and suspected unexpected SARs (SUSARs). IVIG has a well-established side-effect profile. All participants will be monitored for (1) AESIs (includes anaphylaxis, haemolysis, new-onset seizure or abnormal movements not thought to be due to the encephalitis illness, thromboembolism, aseptic meningitis unrelated to the encephalitis illness, acute renal failure and any other medically significant events as determined by the investigator), in the first 5 days following receipt of trial treatment, (2) SAEs up to 6 months after randomisation, or up to 12 months after randomisation where the event is judged directly related to the trial treatment and (3) deaths up to 12 months after randomisation.

Monitoring and reporting of AEs will be performed by the site PI and research team, and will be recorded on the data capture form and uploaded to the eCRF (OpenClinica). The nature and severity of each AE, and the relationship to trial treatment will be documented. The expectedness of an AE will be determined by whether or not it is listed in the SmPC for Privigen or Human Albumin Solution. AESIs and SAEs will be reported to the CI and CSL Behring within 24 hours of the research staff becoming aware. The CI will notify the DSMC of all AESIs and SAEs. This will be expedited (within 24 hours of the CI becoming aware), for all AESIs and for all SAEs that are judged related to the trial treatment. Those that are judged to be unrelated to the trial treatment do not require expedited reporting to the DSMC.

The CI will report all relevant information about a suspected unexpected adverse reaction (SUSAR) that occurs during the course of the trial to the MHRA, CSL Behring, the relevant ethics committee and the DSMC. For fatal and life-threatening SUSARS, this will be performed no later than 7 calendar days after the Sponsor or delegate is first aware of the reaction. Any additional relevant information will be reported within 8 calendar days of the initial report. All other SUSARs will be reported within 15 calendar days. The CI or delegate will also inform all principal investigators concerned of relevant information about SARs that could adversely affect the safety of participants.

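### Expectedness is judged blind against the Privigen and albumin lists combined, so a serious reaction listed only for the product not given escapes the SUSAR report to the MHRA and ethics committee

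*Protocol article*

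**What the plan says.** The active product and the placebo are different substances. Under Interventions, "The IVIG product is Privigen (CSL Behring"), and "The placebo is 0.1% Human Albumin Solution (HAS) in 0.9% Sodium Chloride solution". The Harms section nevertheless gives a single expectedness rule for all participants: "The expectedness of an AE will be determined by whether or not it is listed in the SmPC for Privigen or Human Albumin Solution". It does not tie the reference document to the product a child received.

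Under Blinding, research staff in every aspect of trial conduct "will be blinded to treatment allocation throughout the entire trial period". Unblinding "will occur only in exceptional circumstances when knowledge of the actual treatment received is absolutely essential for further management of the participant", and the decision to unblind "treatment allocation will be solely that of the site investigator". The article gives no other ground for unblinding and no separate route for safety reporting.

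Under Harms, SUSARs go "to the MHRA, CSL Behring, the relevant ethics committee and the DSMC", within 7 calendar days if fatal or life-threatening and otherwise within 15. Two further routes in that section do not depend on expectedness. All AESIs and SAEs go to the CI and CSL Behring within 24 hours of research staff becoming aware. All AESIs and all related SAEs go to the DSMC within 24 hours of the CI becoming aware.

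**The concern.** A serious, suspected-related event becomes a SUSAR only if it is also unexpected, so the expectedness rule decides whether the expedited report is made. If either product's list is enough to make an event expected, whichever product was given, the expected class can only grow compared with a product-specific rule. The error runs in one direction, towards fewer SUSARs.

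The case that matters most is IVIG, the treatment under test. A reaction new to Privigen could be classed as expected because the diluent protein of the placebo happens to list it. At stake is the time-limited report to the regulator and the ethics committee. For an event classed as expected, the article describes no other expedited route to those two bodies.

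**Working it through.** No sample size, rate or event count enters this point. The check is logical: apply the stated rule to each combination of product received and SmPC listing.

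**Inputs**
- Reference rule: listed for Privigen *or* for Human Albumin Solution (Harms).
- Products: Privigen, or 0.1% albumin in saline (Interventions).
- Unblinding: only for participant management, by decision of the site investigator (Blinding).
- SUSAR clock: 7 or 15 calendar days (Harms).

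**Step 1. Which reading of the rule can be applied?** The word *or* could mean the SmPC of whichever product was given, or it could mean either SmPC. Applying the first meaning requires the allocation. Under Blinding, the staff who assess events do not have it and may not obtain it for this purpose. Only the second meaning, the union, is workable as written.

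**Step 2. Compare the rule as written with a product-specific rule**, for a reaction that is serious and suspected to be related.

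| Case | Product given | Listed in | Rule as written | Product-specific rule |
|---|---|---|---|---|
| a | IVIG | Privigen only | expected | expected |
| b | IVIG | albumin only | expected, no SUSAR | unexpected, SUSAR |
| c | placebo | Privigen only | expected, no SUSAR | unexpected, SUSAR |
| d | placebo | albumin only | expected | expected |
| e | either | both | expected | expected |
| f | either | neither | SUSAR | SUSAR |

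The two rules differ in cases b and c. In both, the rule as written loses a SUSAR; in no case does it add one.

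**Step 3. Who is still told in cases b and c?**
- DSMC: yes, within 24 hours of the CI becoming aware, because the event is a related SAE.
- CI and CSL Behring: yes, within 24 hours of research staff becoming aware, because it is an SAE.
- MHRA and ethics committee: no expedited report is described for an event classed as expected.

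**Step 4. How many terms fall in cases b and c?** This would need both SmPCs, and neither is shown. The count runs from zero upwards and cannot be narrowed from the documents.

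**The case against.** The strongest reply is that the consequence is small and partly conjectural. The DSMC's 24-hour route is faster than the SUSAR clock and ignores expectedness, and CSL Behring has an equivalent route. The AESI definition also takes in other events that the investigator considers medically significant. All of this stands. A reader might infer that unexpected IVIG reactions would be hidden from the DSMC or from oversight altogether; the Harms section shows that they would not.

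A second reply is that the effect depends on a serious term being listed for albumin and absent for Privigen, and that nobody has shown one exists. This also stands: the documents support a flaw in the rule, not a demonstrated loss of reports.

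A third reply is that the article condenses a fuller protocol, which may contain sponsor-side unblinding for SUSARs, and that the Harms sentence may simply name one reference per product. This stands in part. A procedure left to the full protocol would be no fault of the article. But the article limits unblinding affirmatively to one ground and one decision-maker, so as worded it excludes such a procedure. If one exists, the Blinding text misstates it and still needs correcting. For the same reason, a reader might conclude that SUSARs are in fact submitted without allocation. That is an inference from the Blinding section; the article does not say it.

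**Conclusion.** The point holds in a limited form. Taken together, the Harms and Blinding sections make expectedness a blind judgement against the union of two product lists. This wrongly classes as expected a serious, suspected-related reaction listed only for the product that the child did not receive. What is lost is the 7- or 15-day report to the MHRA and ethics committee, in two of the six combinations above.

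The conclusion assumes that the article's limits on unblinding are complete as written. Its practical size is unknown and could be nil.

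Two figures might tempt a reader to a larger claim, and neither measures the effect. One is that 154 of the 308 children are to receive IVIG: this counts children exposed, not reports lost. The other is the mass of albumin in the placebo. At 1 g/kg and 10 g/100 mL the volume is 10 mL/kg, and 10 mL/kg at 0.1 g/100 mL is 0.01 g/kg, one hundredth of the immunoglobulin mass. This describes the placebo and says nothing about how often a reaction to IVIG would be misclassified.

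**What to change.** **Harms.** State that expectedness is judged against the SmPC of the product received and that, while allocation is unknown, blinded assessors use the Privigen SmPC alone as the screening reference.

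**Blinding.** Add assessment and regulatory reporting of a suspected SUSAR as a permitted ground for unblinding. It should be done by a non-blinded person independent of the trial. The Oxford staff member already named could serve, but the present remit covers only out-of-hours failure of the randomisation system and must be extended in writing. Because the article has the CI submit SUSARs, that independent person should complete the allocation part of the report, so that the site, the CI and the trial team stay blind.

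**Effect on the cases above.** Case b is screened as unexpected, unblinded off-team and reported. Case d is screened as unexpected, unblinded, found to be placebo and closed as expected. Case c is still missed, because a reaction listed for Privigen passes the screen as expected and is never unblinded. The change therefore repairs the IVIG case and leaves the placebo case open at the screening step.

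**Cost.** A short amendment to two sections, a written extension of one person's remit, an adjusted submission route, and a few more events screened and unblinded away from the trial team. Treatment, follow-up and the efficacy analysis are unaffected.

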### Pregnancy

Although not AEs, pregnancies are reportable events. Should a participant become pregnant during the trial, the trial treatment will be discontinued. Any pregnancy occurring during the clinical trial will be reported to the CI and CSL Behring within 24 hours of the investigator becoming aware and will be followed up for an outcome, which will be recorded. If a congenital abnormality or birth defect is identified, this would fall within the definition of an SAE and will be reported as such.

### Auditing

Regular monitoring by the trial sponsor or delegate will ensure compliance with GCP. The investigator sites will provide direct access to all trial-related source data/documents and reports for the purpose of monitoring and auditing by the sponsor and inspection by local and regulatory authorities. Data will be evaluated for compliance with the protocol and accuracy in relation to source documents. Following written standard operating procedures, the monitors will verify that the clinical trial is conducted and data are generated, documented and reported in compliance with the protocol, GCP and the applicable regulatory requirements. The Quality Assurance manager will also maintain an internal audit programme, which will supplement the external monitoring process to ensure that systems relating to trial conduct, data recording, analysis and reporting are functional are in compliance with the protocol, GCP and the applicable regulatory requirements. The audit programme also includes laboratory activities taking into consideration the MHRA and EMA guidelines for GCP in the laboratory. The Sponsor may carry out audit to ensure compliance with the protocol, GCP and appropriate regulations. GCP inspections may also be undertaken by the MHRA to ensure compliance with protocol and the Medicines for Human Use (Clinical Trials) Regulations 2004.

## Ethics and dissemination

### Ethical and safety considerations

This trial has been approved by the UK National Research Ethics Service (NRES) committee (South Central—Oxford A; REC 14/SC/1416). Clinical trial authorisation has been granted via the Medicines and Healthcare Products Regulatory Agency (MHRA) notification scheme (Ref: 21584/0337/001-0001). Current protocol: V4.0 (10/03/2016). Written approval from the respective Research and Development (R&D) departments will be obtained for each participating site prior to recruitment.

The CI will ensure that this trial (and all subsequent approved amendments) is conducted in accordance with the principles of the Declaration of Helsinki (1996), in full conformity with the International Conference on Harmonisation of Technical Requirements for Registration of Pharmaceuticals for Human Use (ICH) Guidelines for GCP (CPMP/ICH/135/95 July 1996), the Research Governance Framework, and the Medicines for Human Use (Clinical Trial) Regulations 2004. The CI will monitor pharmacovigilance and will report to the Research Ethics Committee (REC), MHRA and funders during and at the end of the trial. All protocol modifications will be disseminated to all relevant parties. The findings of the trial will be presented at national and international meetings and conferences and published in peer-reviewed journals.

### Informed consent and assent

Following identification of a potentially eligible participant by the clinical team, a PIS explaining the trial (including the rationale, aims and objectives, treatment assignation), potential risks and benefits, and all the trial procedures will be provided. Parents/guardians/legal representatives or patients, where appropriate (ie, if the patient has capacity), will be allowed sufficient time to consider the information in the PIS, to seek independent advice and to consider participation in the trial. Informed consent (patients aged 16 years and above) and assent (patients below 16 years) will be obtained by trained research staff using an appropriately signed and dated informed consent/assent form, before any trial-specific procedures are performed. Given that children with encephalitis will be unwell and may be confused during the acute illness, it is likely that eligible patients would be unable to provide consent/assent prior to enrolment. Therefore, for patients aged 16 years and above, informed consent will be obtained from their parent/guardian/legal representative. Once capacity is regained, appropriate consent/assent will be sought from all participants at follow-up time points and if this is not granted, they will be withdrawn from the trial. Participants who previously provided assent but turn 16 years while still in the trial will be required to provide consent for ongoing participation in the trial and will be withdrawn if this is not granted.

Parents/guardians/legally authorised representatives/participants may be approached about a separate, ethically approved, Biobank study and asked if they would like to consent to this study using a separate consent form. Participation in the Biobank is optional and samples will only be stored where appropriate consent has been obtained.

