### Withdrawal

Participants may withdraw from the trial at any time. No further data will be collected. Data collected up until the point of withdrawal from the trial will be analysed unless the parent/participant decides against this. If a participant is withdrawn due to an AE, the investigator will follow this up until it resolves or stabilises. All participants who are withdrawn from trial treatment (see the Withdrawal from trial treatment section) will remain in the trial and followed up as per the trial protocol, but will not have any invasive procedures performed. The trial data will be analysed on an intention-to-treat (ITT) basis; therefore, all withdrawals, either from the trial or from the trial treatment, will be reported and included in the data analyses. All protocol deviations will also be reported.

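### A child who regains capacity and declines assent or consent is withdrawn with no further data, so this route loses the 12-month GOSE-Peds only among children who regain capacity; the turning-16 rule has no capacity condition

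*Protocol article*

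**What the plan says.** All references are to the Protocol article.

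- **Entry.** Informed consent and assent states that "it is likely that eligible patients would be unable to provide consent/assent prior to enrolment". Enrolment then rests on the parent, guardian or legal representative, and this includes patients of 16 and above.
- **Capacity regained.** The same section says that consent or assent is then "sought from all participants at follow-up time points and if this is not granted, they will be withdrawn from the trial". Table 2 marks discharge (T3), 6 months (T5) and 12 months (T6) as the times for doing this where it has not been obtained before.
- **Turning 16.** "Participants who previously provided assent but turn 16 years while still in the trial will be required to provide consent for ongoing participation", and they are withdrawn if it is not granted. This sentence does not mention capacity.
- **Effect of leaving the trial.** Withdrawal: "Participants may withdraw from the trial at any time. No further data will be collected". Earlier data are kept: "Data collected up until the point of withdrawal from the trial will be analysed unless the parent/participant decides against this".
- **Contrast.** Participants withdrawn only from trial treatment "will remain in the trial and followed up as per the trial protocol", without invasive procedures.
- **Outcome schedule.** Table 2 and Questionnaires and outcome measures place GOSE-Peds at 6 and 12 months only. Primary analysis also names data at discharge, but no GOSE-Peds is scheduled then.

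**The concern.** Read together, these rules select who can be lost. A child who never regains capacity is not asked and stays in on the parent's consent. Only a child who recovers enough to be asked can leave by this route, and that child's 12-month primary outcome goes too. Regaining capacity should be related to neurological recovery, which the primary outcome measures, so the loss may not be missing at random.

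The repeated-measures model in Statistical methods uses whatever was observed. For a child who declines at discharge it has no GOSE-Peds to use. There is a tier that keeps follow-up after stopping treatment. There is none for a family willing to give the outcome interview after the child has declined everything else.

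The turning-16 sentence raises a smaller, separate issue. Read literally, a teenager who once assented but lacks capacity at 16 cannot grant consent and is withdrawn. A patient who is already 16 at enrolment and lacks capacity is kept on a parent's consent.

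**Working it through.** **Inputs from Sample size.** Good recovery 43% in control, difference 20 points (so 63% on IVIG), 154 per group, about 10% attrition, 90% power, two-sided 5%.

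**The plan's own figure.** The two-proportion formula with continuity correction for 43% v 63% gives 139 per arm. 139 / 0.90 = 154.4, so 154 or 155 per arm and 308 to 310 in total. The stated 308 reproduces, and the sample size is not at issue.

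**Assumptions.** The documents give no refusal rate. Let g be the proportion declining among children with good recovery and b the proportion among the rest, each the same in both arms. For true rate p:

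- proportion lost = pg + (1 − p)b
- observed rate = p(1 − g) / [1 − pg − (1 − p)b]

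These are rates among children with an observed outcome. They are not the output of the mixed model.

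**Example, g = 10%, b = 0.**
- Control: 0.43 × 0.90 / (1 − 0.043) = 0.387 / 0.957 = 40.4%. Lost: 154 × 0.043 = 6.6 children.
- IVIG: 0.63 × 0.90 / (1 − 0.063) = 0.567 / 0.937 = 60.5%. Lost: 154 × 0.063 = 9.7 children.

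**Range, b = 0.** Differences are from unrounded rates. Power is without continuity correction.

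| g | Lost, control / IVIG | Observed rates | Difference (points) | Power, no other loss | Power, 10% other loss |
|---|---|---|---|---|---|
| 5% | 2.2% / 3.2% | 41.7% / 61.8% | 20.0 | 93.9% | 91.4% |
| 10% | 4.3% / 6.3% | 40.4% / 60.5% | 20.1 | 93.3% | 90.6% |
| 20% | 8.6% / 12.6% | 37.6% / 57.7% | 20.0 | 91.8% | 88.9% |
| 30% | 12.9% / 18.9% | 34.6% / 54.4% | 19.8 | 89.9% | 86.6% |

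On the same basis, power without this route is 94.4% with no other loss and 92.0% with 10% other loss.

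**Why the contrast holds.** The observed odds in an arm are [p / (1 − p)] × (1 − g) / (1 − b). If g and b are equal in both arms, the last factor cancels and the odds ratio stays at (0.63 / 0.37) / (0.43 / 0.57) = 2.257. This also holds when some children without good recovery decline: g = 10% and b = 5% gives 41.7% v 61.7%, a difference of 20.1 points.

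**Children too young to be asked.** If, as an assumption, half of the children with good recovery could be asked and 10% of those declined, the effective g is 5%. That is the first row of the table: 41.7% v 61.8%.

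**Attrition allowance.** The mean true rate is (0.43 + 0.63) / 2 = 0.53. With b = 0, this route alone would use the whole 10% at g = 0.10 / 0.53, about 19%.

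**Outcome data left by time of refusal.** A refusal at T3 comes before any GOSE-Peds. A refusal at T5 before the interview also leaves none. A refusal at T6 can lose the 12-month value but leaves the 6-month one.

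**Turning 16.** Every participant aged 15 at randomisation reaches 16 within 12 months, but the rule reaches only those who had already assented. The documents give no count.

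**The case against.** Seeking the child's own agreement is an ethical requirement in a trial with ethics approval, and ending participation when a capable child declines is a legitimate choice. That stands. Follow-up on the parent's word against the child's refusal would be an ethical trade-off, so any change must be an offer that both can refuse.

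Several limits on size also stand. Infants and toddlers cannot decline, and two of the five age strata are under 5. A child may regain capacity and still score above 2, so the link to the endpoint is indirect. Data up to withdrawal are normally kept, and Withdrawal already requires all withdrawals to be reported. Statistical methods plans sensitivity analyses under different missing-data assumptions, and the unseen analysis plan may include one for data not missing at random. None of this restores an outcome that was never collected.

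A reader might infer that the rule biases the treatment comparison. That would need refusal, given outcome, to differ between arms. An invented split of 5% on placebo and 15% on IVIG gives 41.7% v 59.1%, a difference of 17.4 points; the reverse split gives 39.1% v 61.8%, or 22.7 points. The documents support neither split. Families and research staff are blinded with a visually identical placebo. Harms mentions the known side-effect profile of IVIG but does not tie it to refusal.

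On turning 16, the paragraph elsewhere speaks of capacity, and consent not being granted may simply mean refused. That reading is plausible, but the sentence does not say so.

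**Conclusion.** The point holds in a limited form. As written, the consent and withdrawal rules discard later primary outcome data only for children who regain capacity, and a refusal at discharge leaves no GOSE-Peds.

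The size is unknown. Under an assumed 5% to 30% refusal confined to good recoveries and equal across arms, each arm's good-recovery rate is understated by about 1 to 9 points, and less once children too young to assent are left out. With 10% other loss, power falls from 92.0% to between 91.4% and 86.6%. The odds ratio is unchanged and the difference is within 0.2 points of 20. The documents do not show a biased treatment contrast.

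The turning-16 sentence is a drafting gap that sits badly with the acceptance of parental consent for patients already 16 at enrolment. Its trigger is a birthday, not recovery, and few children are affected. Both parts should be changed; neither undermines the trial.

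**What to change.** Subject to ethics approval:

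1. Replace automatic full withdrawal with a tiered option. When a child declines, stop all procedures and ask the child and the parent whether they agree to limited follow-up only: a blinded GOSE-Peds interview with the parent at 6 and 12 months, and vital status. If they do not agree, withdraw the child fully, as now.
2. Make the turning-16 rule conditional on capacity. Where capacity is lacking, the consent of the parent or legal representative continues.

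The cost is an amendment to the consent section and the information sheets, with ethics review. No visits are added. Some families will still choose full withdrawal, so the loss is reduced but not removed.
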